## 9.2 Online questionnaires

They will be applied through the online platform "Qualtrics". The technical details of the questionnaires to be completed by the participants are specified below.

### 9.2.1 Block of pre-post programme questionnaires (Table 1)

**Table 1. Questionnaires to be completed by pre-post program participants**

| Construct                      | Instrument                                                                                                          |
|--------------------------------|---------------------------------------------------------------------------------------------------------------------|
|                                | Sociodemographic and health data*                                                                                   |
|                                | Previous experience in meditation                                                                                   |
|                                | Impact of COVID-19 on Students                                                                                      |
|                                | Mindfulness and compassion                                                                                   |
| Mindfulness                    | Five Facet Mindfulness Questionnaire (FFMQ; Baer et al., 2006) → short version of 20 items                          |
| Compassion for oneself         | Self-Compassion Scale (SCS-SF; Raes et al., 2011) → Short version of 12 items                                       |
| Compassion for others          | CS Pommier Compassion Scale (CSP; Pommier et al., 2020) 24 items→                                                   |
| Empathy                        | Interpersonal Reactivity Index (IRI, Davis, 1980) 14 items (subscales of empathic concern and personal discomfort)→ |
|                                | Psychopathology                                                                                              |
| Stress, anxiety and depression | Depression Anxiety Stress Scales (DASS – 21; Lovibond, & Lovibond, 1995) 21 items.→                                 |
| Emotional regulation           | Difficulties in Emotion Regulation Scale (DERS, Gratz & Roemer, 2004) 28 items→                                     |
| Burnout                        | Maslach Burnout Inventory (student version) 15 items→                                                               |
|                                | Welfare                                                                                                      |
| General well-being             | Pemberton Happiness Index (PHI, Hervas, & Vazquez, 2013) 11 items→                                                  |
| Resilience                     | Brief Resilience Scale (BRS; Smith et al., 2008) 5 items→                                                           |

### 9.2.2 Block of inter-sessional questionnaires (once a week)

The inter-session evaluations will consist of a brief questionnaire aimed at evaluating adherence to the program and weekly practice. In addition, at the equator and at the end of the program, the participant will complete an anonymous survey required by the Compassion Institute to evaluate the partnership with the program, the alliance with the instructor and the satisfaction with the program. In addition, to ensure and evaluate adherence to the protocol by the instructor, the sessions of the program will be recorded for later review.

## 10. MAIN OBJECTIVE

### Main objective

The objective of this proposal is to evaluate the efficacy and psychological changes produced by a standardized program of Training in the Cultivation of Compassion (CCT®)

in medical students of the Complutense University of Madrid compared to a control group on the waiting list.

### **Secondary objectives**

- 1) Examine whether the changes produced by the program are maintained two and six months after the end of the program.
- 2) Examine changes in psychological mechanisms mediating positive program outcomes. To assess whether compassion training is a protective factor against the stress and psychological distress caused by the COVID-19 pandemic.

## **11. EXPERIMENTAL DRUG AND CONTROL. DOSAGE, FITNESS, VIA**

### **11.1 Choice of CST programme**

The CCT® program was developed in 2009 at Stanford University by contemplative scholars, clinical psychologists and researchers, and is currently sponsored by the Compassion Institute. CCT® is a secular program that integrates traditional contemplative practices with contemporary psychology and scientific research on compassion. The CCT® is an 8-week blended course that combines a 2-hour face-to-face session each week with internships during the week. The goal of the CCT® in medicine is to develop a compassionate mind and heart that provides skills for self-care and fosters compassionate interaction with patients.

Compassion, defined as sensitivity to one's own suffering and that of others, along with a deep commitment to seek to alleviate it, is a basic capacity for care inherent in the human being that allows one to respond to suffering with understanding, patience and kindness, rather than with fear and repulsion. Compassion can be trained (Stepien, 2006; Hojat, 2009a, Goetz, 2010; Kelm, 2014), and through his practice, improve compassion for oneself and extend it to those people who are difficult for us. The CCT™ program is based on developing a genuine compassion that arises from recognizing that the suffering of others is similar to our own and that like us, others also wish to be free from such suffering. From this statement, emerges the empathic concern that sensitizes us to the pain of others. Far from implying pity (it places the one who experiences it in a situation of superiority), condescension, permissiveness, or absence of limits, compassion is related to the courage to face suffering and remain in the face of it, and with the motivation to do something to diminish it.

### **11.2 Program Details**

The CCT® program consists of 6 steps that are developed in eight weeks. Specifically:

*Week 1. Settlement and approach*

Development of mindfulness, settling the mind on the present experience with acceptance and without judgment through exercises aimed at focusing attention on the breath by loving, with kindness, attention back whenever it is distracted.

*Week 2. Compassion as a natural capacity*

Learn to recognize the physical and psychic signs associated with compassion through dialogue and guided exercises.

*Week 3. Self-pity*

It presents the idea that the cultivation of self-compassion is the basis for developing compassionate behavior towards others. Training in the practice of self-compassionate dialogue, self-acceptance and growth of these skills in difficult situations.

*Week 4. Self-love*

Learn to cultivate warmth, appreciation, joy and gratitude for oneself.

*Week 5. Shared humanity*

Recognition of shared humanity (seeing the other "just as I am") and interdependence as the foundation of compassion toward others.

*Week 6. Compassion*

From shared humanity and interdependence, cultivate compassion for all beings, including difficult ones.

*Week 7. Active compassion*

Aimed at developing inner stability to welcome the suffering of others and offer one's own happiness.

*Week 8. Integrated Compassion Cultivation Practice*

Bring together the elements of the previous steps into a compassionate meditation practice that can be followed as a daily practice

These six steps will be developed through:

- 8 weekly meetings of 2h online duration (due to COVID-19) consisting of relational exercises, meditations and dialogues on pedagogy and science related to the theme of the week. The online meetings will be held through the Zoom platform.
- Guided meditations recorded in audios of 20-30 min duration to be carried out daily (formal practices).
- Informal practices in everyday life

**11.3 Procedure for assessing participant compliance**

Inter-session surveys together with the number of sessions attended by the participant will be used to assess adherence to the program.

## **12. PRIMARY ENDPOINT**

- Main variables:
  - Psychological distress: stress, anxiety, depression.
  - Psychological well-being.
  - Burnout
  - Compassion
- Secondary variables:
  - Mindfulness or attention to the present.
  - Empathy.
  - Emotional regulation.
  - Resilience.
  - Adherence to the program.
  - Daily practice.

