#### **8.4. Hypothesis**

1. The standardized Compassion Cultivation Training (CCT) program will produce an improvement in emotional well-being and a reduction in psychological distress (stress, anxiety, depression) and burnout of post-program medical students compared to a control group on the waiting list.
2. Such changes shall be maintained over time two and six months after the end of the programme.
3. The above changes will be driven by increases in compassion for oneself, compassion for others, attention to the present moment, and emotional regulation skills.
4. The skills developed in the program will be a protective factor for the management of stress and psychological distress caused by the COVID-19 pandemic.

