## **13. STUDY POPULATION AND TOTAL NUMBER OF PATIENTS**

### **13. 1. Sample calculation method**

The sample size was determined a priori using the G\*Power software (v. 3.0.10). The sample size required to analyze a mixed ANOVA (the group factor as an independent measure and the time factor as a related measure), with an expected effect size of 0.40 (Brito-Pons et al., 2018), a significance level of 0.05, and a power of 90%, the estimated sample size is 44 participants in the entire sample (22 in each group). This estimation of the sample size has been carried out for the pre-post change in the variable of emotional distress (i.e., stress, anxiety and depression).

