#### **14. STATISTICAL ANALYSIS**

Following the CONSORT recommendations, Intention-To-Treat Analysis will be performed to handle lost data. A diagnosis of the randomness pattern of the loss will begin using Little's MCAR test. The baseline differences between completers (i.e., per-protocol) and missing will also be analyzed to determine if there are any variables in the dataset that predict data loss. Depending on the loss pattern, multiple imputations will be made or by means of Maximum Likelihood algorithms. Finally, sensitivity analyses will be performed comparing the per-protocol data with the imputed ones to determine if the imputation has generated biased estimates. As indicated in the previous section, the criterion of attendance at 75% of the sessions of the program will be used as an indicator of "minimal exposure to treatment".

Student's t-tests and chi-square tests will be used to analyze differences between groups at baseline. The main analysis will be a mixed ANOVA with two factors: independent measures group factor (experimental vs control) and repeated measures time factor (pre, post, follow-up 2 and 6 months). ANCOVAs will also be performed using baseline as a covariate in analyses and repeated measure ANOVAs to assess the maintenance of changes over time. The analysis of variance will be complemented by mediating and moderating analyses to study the mechanisms of change of the program. A significance

level of alpha 0.05 will be defined in bilateral contrasts. Statistical analyses will be carried out using SPSS (v. 25) and R (v. 3.6.1) software.

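### Section 12 lists four unranked main variables (four to seven scores) at a single 0.05 level, while the sample size covers emotional distress only, so the protocol does not fix what makes the trial positive

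*Protocol*

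**What the plan says.** Protocol section 12 separates main from secondary variables, but within the main group it gives four items with no order: "Psychological distress: stress, anxiety, depression", well-being, burnout and compassion. Table 1 in section 9.2.1 measures compassion with two instruments, one for compassion towards oneself and one for compassion towards others.

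Section 14 names a mixed ANOVA over four measurement times as the main analysis, adds ANCOVAs and mediation analyses, and sets a single significance "level of alpha 0.05 will be defined in bilateral contrasts". It mentions neither an order of testing nor an adjustment.

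Section 13.1 derives 44 participants (22 per group) "with an expected effect size of 0.40", alpha 0.05 and 90% power, and adds: "This estimation of the sample size has been carried out for the pre-post change in the variable of emotional distress".

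In section 8.4, hypothesis 1 concerns well-being, distress and burnout. Hypothesis 3 states: "The above changes will be driven by increases in compassion for oneself, compassion for others", followed by present-moment attention and emotional regulation.

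**The concern.** A section on the primary endpoint should let a reader say, before the data are seen, which result decides the trial. This one does not. The sample size points to distress, the list of main variables points to four constructs, and the main objective in section 10 speaks generally of efficacy and psychological changes. After the data are in, whichever main variable falls below 0.05 could be presented as the efficacy result, and the stated 5% error rate would no longer describe that claim.

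The second matter is the place of compassion. It ranks as a main outcome in section 12, yet section 8.4 treats it as a mechanism. The other two mechanisms named in hypothesis 3 are only secondary variables. A report could therefore present a rise in self-rated compassion as success on a main variable while none of the outcomes in hypothesis 1 had moved.

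**Working it through.** **Inputs**
- Main variables: protocol section 12; instruments from Table 1, section 9.2.1.
- Alpha: 0.05 two-sided, section 14.
- Correlation between main variables: not given. Assumed equal for all pairs, 0 to 0.7.
- Rule for declaring success: not given. The error rates in steps 3 and 4 assume that any one significant main variable counts.

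**1. The plan's own figure.** The protocol gives no familywise error rate, only N = 44. A noncentral F calculation for a between-group test with f = 0.40, m = 4 measurements and an assumed correlation of 0.5 between times gives

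lambda = f² × N × m / (1 + (m − 1) × rho) = 0.16 × 44 × 4 / (1 + 3 × 0.5) = 28.16 / 2.5 = 11.26, with 1 and 42 degrees of freedom, and power 0.906.

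So 44 can be reproduced, for one variable tested at 0.05. The effect-size metric and the correlation are not stated, so this is one possible route. A group-by-time test on two measurements, with f = 0.40 and correlation 0.5, would need only 20.

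**2. Number of scores.** Well-being and burnout are taken as one score each.
- Distress as one, compassion as one: 1 + 1 + 1 + 1 = 4
- Distress as one, compassion as two: 1 + 1 + 1 + 2 = 5
- Distress as three, compassion as one: 3 + 1 + 1 + 1 = 6
- Distress as three, compassion as two: 3 + 1 + 1 + 2 = 7

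**3. Independent tests.** P(at least one false positive) = 1 − 0.95^k:
- k = 4: 1 − 0.8145 = 18.5%
- k = 5: 1 − 0.7738 = 22.6%
- k = 6: 1 − 0.7351 = 26.5%
- k = 7: 1 − 0.6983 = 30.2%

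**4. Correlated tests.** For k two-sided z-tests with common correlation r, the probability is 1 − E[p(Z)^k]. Here Z is standard normal and p(Z) = Φ((1.96 − √r Z)/√(1 − r)) − Φ((−1.96 − √r Z)/√(1 − r)), evaluated by quadrature.

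| Scores | r = 0 | r = 0.3 | r = 0.5 | r = 0.7 |
|---|---|---|---|---|
| 4 | 18.5% | 17.4% | 15.6% | 13.0% |
| 5 | 22.6% | 20.9% | 18.3% | 14.8% |
| 7 | 30.2% | 27.2% | 23.0% | 17.8% |

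The range is 13.0% to 30.2%. At r = 0.8 the figures for four and seven scores fall to 11.4% and 14.9%, still more than twice 5%.

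**5. The opposite rule.** If every main variable had to be significant, the false-positive rate for the joint claim could not exceed 5%. The figures in steps 3 and 4 therefore depend on the any-one rule.

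**6. Roles of compassion, side by side.** Section 12: main variable. Hypothesis 1: not named. Hypothesis 3: driver of the changes in hypothesis 1. Present-moment attention and emotional regulation, drivers in the same hypothesis, are secondary in section 12. The placement is inconsistent, but it changes neither k nor r, so it does not enter the error rate.

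**The case against.** The strongest reply is that no passage says one significant score establishes efficacy. Hypothesis 1 joins its outcomes with 'and', and if all were required there would be no inflation. This stands in part: the error rate is conditional. But the protocol does not adopt the stricter rule either, and section 12 ranks nothing.

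A reader might infer that there are at least seven tests and that the risk is therefore 18% to 30%. The documents do not support seven as a floor. Section 12 gives distress a single bullet and section 13.1 calls it a single variable, so four or five scores are equally possible.

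A reader might also infer that compassion's double role raises the false-positive risk. It does not. A mediator has to respond to the intervention, so testing it as an outcome is legitimate, and a course in compassion may reasonably list it as a main variable. Nor can a gain in compassion alone confirm hypothesis 1, which does not name it. What remains is that section 12 leaves room to report it as a main result.

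Nor should the figures simply be raised for the measurement times and the ANCOVAs. Section 14 names one main analysis with all times in one factor, and the ANCOVAs are additional.

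Finally, multiplicity procedures are often left to the statistical analysis plan, which is not shown here and may contain one. That answers the absence of an adjustment. It does not answer a primary-endpoint section that names four main variables and no primary one.

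**Conclusion.** The point holds as a weakness in how the protocol fixes its primary endpoint: four unranked main variables, one 0.05 level, and a sample size tied to one of the four. If any one significant result is reported as efficacy, the chance of at least one false positive is about 13% to 30% instead of 5%. This rests on four to seven tests, on equal correlations of 0 to 0.7 that the documents do not give, and on a success rule that they neither state nor exclude. Under an all-required rule there is no inflation.

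The conflicting role of compassion between sections 8.4 and 12 is a separate inconsistency with no effect on these figures. The whole matter is a cheap improvement that settles what the trial can claim.

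**What to change.** - In section 12, name one primary endpoint: emotional distress as one score (for example the DASS-21 total; section 13.1 does not name a score), compared between groups at post-programme. This is the variable and the pre-post contrast that section 13.1 already describes.
- Treat the other main variables as key secondary, with Holm adjustment, and say so in section 14.
- State that a gain in compassion alone does not establish efficacy under hypothesis 1. Whether compassion also leaves the main variables is a matter of judgement and is not required.
- If mediation uses 2-month outcomes, state that they are collected before the controls start the course. Section 9.1 offers controls the course 2 months after the first programme ends, the same point as the 2-month assessment, and does not say which comes first.

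**Cost.** Wording only; this change does not alter the sample size in section 13.1. The other main variables face a stricter threshold and cannot carry the efficacy claim alone. With four key secondary scores (well-being, burnout and the two compassion scores), the smallest p-value would be compared with 0.05/4 = 0.0125.

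The alternative, keeping seven co-equal scores under Bonferroni, gives 0.05/7 = 0.0071 each. In the calculation that reproduces 44, power then falls from about 91% to about 70%, and about 66 participants would be needed for 90%. That loss depends on the variant: for the two-measurement group-by-time test, power at 44 would stay near 99%.

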## **13. STUDY POPULATION AND TOTAL NUMBER OF PATIENTS**

### **13. 1. Sample calculation method**

The sample size was determined a priori using the G\*Power software (v. 3.0.10). The sample size required to analyze a mixed ANOVA (the group factor as an independent measure and the time factor as a related measure), with an expected effect size of 0.40 (Brito-Pons et al., 2018), a significance level of 0.05, and a power of 90%, the estimated sample size is 44 participants in the entire sample (22 in each group). This estimation of the sample size has been carried out for the pre-post change in the variable of emotional distress (i.e., stress, anxiety and depression).

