### **13.2. Estimation of possible loss**

In order to minimize the sample loss throughout the study, we have adopted several measures aimed at maintaining motivation and reinforcing the participation of the participants: the members of the control group will sign an agreement to carry out the relevant evaluations to formalize the reservation of their place in the second promotion of the course. Once the study is completed, participants will be rewarded with an ECTS credit of free configuration (approved by the UCM Studies Commission on November 12, 2020) and object of academic recognition for the degree in medicine. In addition, participants who complete all evaluations of the study will receive a gift book on the theme of the program. For all the above, we expect a sample loss of less than 5%.

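### The sample size of 44 for 90% power at an effect size of 0.40 does not follow from the pre-post test that section 13.1 describes

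*Protocol*

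**What the plan says.** Section 13.1 of the protocol bases the sample size on G*Power and "a mixed ANOVA (the group factor as an independent measure and the time factor as a related measure"), "with an expected effect size of 0.40" taken from a cited study, an alpha of 0.05, and "a power of 90%, the estimated sample size is 44 participants in the entire sample (22 in each group"). The same paragraph names the target: "This estimation of the sample size has been carried out for the pre-post change in the variable of emotional distress", that is, stress, anxiety and depression.

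Section 14 makes the main analysis a mixed ANOVA with a "repeated measures time factor (pre, post, follow-up 2 and 6 months"), and adds ANCOVAs with baseline as covariate. Tests are two-sided: "level of alpha 0.05 will be defined in bilateral contrasts". Section 13.2 adds "we expect a sample loss of less than 5" per cent.

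Four inputs to the calculation are not given: the ANOVA effect being powered (group, time or group by time), the metric of 0.40, the number of measurements entered, and the correlation between them.

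**The concern.** The first hypothesis in section 8.4 compares the programme with the waiting list after the programme. For a pre-post change in a two-arm mixed ANOVA, the effect that answers it is the group-by-time interaction with two measurements. In G*Power the ANOVA effect size is Cohen's f. Read that way, the inputs of section 13.1 should return a total well below 44.

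The 90% is the protocol's only statement of how informative the trial will be on distress, which section 12 lists among the main variables. If the figure belongs to another test or another metric, nobody can judge what a null result on distress would mean.

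**Working it through.** **Inputs from the protocol.** Two arms, 1:1 (section 9); effect size 0.40, alpha 0.05, power 0.90, N = 44, pre-post change (section 13.1); two-sided tests and four time points in the main analysis (section 14).

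**Assumptions.** The correlation rho is not stated, so a range is shown. Sphericity is assumed and N is an even total.

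**Formulas** (noncentral F, G*Power parameterisation, m measurements):
- Group by time: λ = f²·N·m/(1−rho), with m−1 and (N−2)(m−1) df.
- Group main effect: λ = f²·N·m/(1+(m−1)·rho), with 1 and N−2 df.
- In a balanced 2×2 interaction, an arm difference in change of D SD puts an effect of ±D/4 in each cell, so f = D/4.
- ANCOVA on the post score: λ = N·D²/(4(1−rho²)).

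**1. Reproducing 44 for the described test, 0.40 as f (m = 2).**

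| rho | N for 90% power |
|---|---|
| 0 | 36 |
| 0.3 | 26 |
| 0.5 | 20 |
| 0.7 | 14 |

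The required N falls as rho rises from 0, so no non-negative correlation gives 44. At N = 44 and rho 0, λ = 0.16×44×2/1 = 14.08 and power is 0.956. At rho 0.5, λ = 28.16 and power is 0.999. An f of 0.40 means D = 4×0.40 = 1.6 SD.

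**2. 0.40 as an arm difference in change, in SD units.** Then f = 0.40/4 = 0.10.
- Interaction, rho 0.5: λ = 0.01×88/0.5 = 1.76; power 0.254; 90% would need N = 266.
- Interaction, rho 0.7: λ = 0.88/0.3 = 2.93; power 0.387; 90% would need N = 160.
- ANCOVA, rho 0.5: λ = 44×0.16/(4×0.75) = 2.35; power 0.322; 90% would need N = 200.
- ANCOVA, rho 0.7: λ = 1.76/0.51 = 3.45; power 0.442.

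**3. 0.40 as Cohen's d, entered as f = d/2 = 0.20.**
- rho 0.5: λ = 0.04×88/0.5 = 7.04; power 0.736.
- rho 0.7: λ = 3.52/0.3 = 11.73; power 0.917.
- At rho 0.69 the required N is exactly 44 (power 0.909).

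However, f = d/2 is the conversion for a simple two-group mean comparison. In the 2×2 interaction, f = 0.20 is an arm difference in change of 4×0.20 = 0.80 SD, twice the 0.40 it would stand for.

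**4. Another calculation that returns 44.** Group main effect, four measurements, f = 0.40, rho 0.5: λ = 0.16×44×4/2.5 = 11.26; power 0.906, and 0.8996 at N = 43. The match depends on rho: N is 34 at 0.3 and 54 at 0.7. A group main effect over two measurements with f = 0.40 and rho 0.25 also returns 44.

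**5. What 44 analysed can detect at 90% power.** With 1 and 42 df, λ must be about 11.01.
- Pre-post interaction: D = √(8(1−rho)×11.01/44), which is 1.00 SD at rho 0.5 and 0.775 SD (0.78 rounded up) at rho 0.7.
- ANCOVA: D = √(4(1−rho²)×11.01/44), which is 0.87 SD at rho 0.5 and about 0.715 SD (0.72 rounded up) at rho 0.7.

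**6. Loss.** 44×0.95 = 41.8, so about 42 completers at a 5% loss.

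**The case against.** The strongest reply is that section 13.1 leaves the metric and the correlation open, so its inputs cannot be said outright to exclude 44. If 0.40 was treated as d and entered as f = 0.20, the pre-post interaction returns exactly 44 at rho 0.69. As arithmetic that stands. It does not rescue the planning claim, because the f used would then represent 0.80 SD on the tested contrast, not 0.40.

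A reader might infer more than the protocol supports in three ways:

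- **That 44 was computed as a group main effect over four measurements.** The numerical match is exact at rho 0.5, and section 14 does have four time points. But the protocol nowhere says this was run, rho 0.5 is assumed, and other routes also return 44. It is a possible origin only. What can be said is that such an effect averages in the baseline and the follow-ups, so it is not the pre-post change.
- **That the trial is underpowered.** The 25% and the N of 266 hold only if 0.40 is an arm difference in change in SD units, which the protocol does not say. With 0.40 as f, 44 is more than enough.
- **That ignoring dropout undermines the size.** The expected loss is below 5% and section 14 plans an intention-to-treat analysis that handles missing data. In the four-measurement calculation, going from 44 to 42 lowers power only from 0.906 to 0.892. This is a minor point.

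It is also fair to say that the mixed ANOVA is the planned main analysis. The correction should not replace it with ANCOVA.

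**Conclusion.** The point holds in limited form: the stated pair of N = 44 and 90% power for 0.40 does not follow from the pre-post test described. With 0.40 as f, the number is wrong for that test (14 to 36 needed for rho from 0.7 down to 0). With 0.40 as an SD difference between arms in change, the power is wrong (about 25% to 39% for rho 0.5 to 0.7; 32% to 44% by ANCOVA). The f = 0.20 reading gives 74% to 92% over the same correlations, but for a difference of 0.80 SD. At rho 0.5 alone, power for the named comparison runs from 25% to over 99% depending on a metric that is not stated.

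The 90% is therefore unsupported, not shown to be too high or too low. These figures assume sphericity, equal arms, 44 analysed and the correlations shown. The protocol gives no correlation of its own.

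**What to change.** Keep N = 44 and rewrite section 13.1.

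1. Name the powered effect as the group-by-time interaction from pre to post, with two measurements, since that answers the pre-post hypothesis.
2. State the metric of 0.40 and, if it is converted to f, the conversion used.
3. State the assumed pre-post correlation and show a range around it.
4. Give the resulting power, or the detectable difference at 90% power with 44 analysed: about 1.00 SD (rho 0.5) and 0.78 SD (rho 0.7) for the interaction. The corresponding figures for the ANCOVA already planned in section 14, 0.87 and 0.72 SD, can be added beside them.
5. Remove the claim of 90% power for 0.40 unless the named test and metric reproduce it.
6. Note that a loss of up to 5% leaves about 42 completers.

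The cost is one paragraph and possibly a less favourable stated figure. No extra enrolment and no change to the main analysis are needed.
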